### Outcome measurements

2.8.

Patients must have an indication for the surgery. The primary outcome variable is the JOA score. The secondary outcome variables include the VAS score, physical examination findings, length of hospital stay, expenses, and complications. Outcomes will be measured on the first postoperative day, and thereafter at the 1st week, and at 1, 3, 6, 12, and 24 months after surgical treatment. A physical examination will be conducted after 1 week, 1 month, and 12 months from the day of the surgery (Table 1). The non-inferiority margin for the primary outcome is five.

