## Introduction

1.

Although spinal intradural extramedullary (IDEM) tumors grow slowly, the spinal canal is limited by its small volume, and the spinal cord and nerve roots are compressed or invaded by the tumor, which causes sensory, motor, and autonomic dysfunction (1). The treatment of spinal IDEM tumors focuses on removing tumor tissue and decompressing the nerve root and spinal cord to improve nerve function (2, 3). Traditional surgical methods include laminectomy (total laminectomy and hemilaminectomy), laminotomy, and laminoplasty (LP) (4). Among the available spinal surgeries with different indications, a “standard surgical procedure” for treating spinal IDEM tumors has not been determined. Owing to the development of minimally invasive spine surgery (MISS), the paraspinal mini-tubular technique (PMTT) has been introduced for treating IDEM tumors (5–7). Most studies reported that tubular spine surgeries reduced the volume of estimated blood loss (EBL) and shortened the length of hospital stay. The postoperative outcome of the patients was good, with fewer complications. These together promoted the development of MISS. A microscope-assisted PMTT has a larger operating space than endoscopy and a relatively wide range of indications, including various types of intervertebral disc herniation, spinal stenosis, spinal tumors, and spinal cord injuries (8). With the popularization and application of PMTT, the safety and effectiveness of treating spinal-related diseases have been increasingly recognized. Compared with traditional surgery, the microscope-assisted microtubular technique has the advantages of less tissue damage, fewer complications, shorter length of hospital stay, reduced postoperative pain, improved surgical efficiency, and reduced risk of spinal instability (9–11). To the best of our knowledge, prospective, randomized controlled trial studies with a large sample comparing the safety and effectiveness of the PMTT and LP in the treatment of spinal IDEM tumors, have not been conducted. Therefore, this study aims to explore the difference in the therapeutic effect of the PMTT and LP in the treatment of patients with spinal IDEM tumors through a prospective, multi-centered, non-inferiority randomized clinical trial. The main hypothesis is that PMTT has advantages in cost-effectiveness, and it is equivalent in safety and efficacy to LP.

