### Primary outcome

2.9.

We will use the JOA score to assess the primary outcome (12, 13). It is divided into the cervical and JOA scores, including subjective symptoms, clinical signs, daily activities, and bladder function. Each item had one or more problems. The total score of the JOA was 29, and the total JOA score of the cervical spine was 17. The lower the score, the more obvious the dysfunction. The outcome parameters will be assessed using validated questionnaires and physical examination. Data from the questionnaires will be collected at 1 week and at 1, 3, 6, 12, and 24 months after the surgery by the research nurse.

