### Sample size calculation

2.11.

The sample size for this study was calculated based on the JOA scores. Based on the preliminary data of our department, the mean difference and SD for the JOA used in the sample size calculation were as follows: mean 21.7, SD 5.8. The sample size for non-inferiority trials was calculated using the following: (1) significance level (alpha) of 0.05 and (2) power (beta) of 90%. We estimated that 112 patients would need to be included in each group. Accounting for 10% attrition and the actual situation of each participating center, 280 patients will be recruited in total. We intend to recruit patients within two years. Recruitment for the study began in October 2021.

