### Statistical analysis

2.12.

All data will be analyzed according to the intention-to-treat principle (16, 17). The baseline data will be compared and analyzed using descriptive statistics [mean (SD), proportion, or median (range)] to determine whether balanced groups were obtained after randomization. Student's *t*-test or Mann–Whitney's *U* test will be used to compare continuous variables. Categorical variables will be compared using *χ*^2^ or Fisher's exact tests. All comparative analyses will be reported with point estimates [means (SD) or odd ratios (ORs)], 95% CIs, and *p*-values. Statistical significance will be set at *p *< 0.05. Non-inferiority margins will be set as listed in Table 2. Statistical analysis will be performed using appropriate statistical software (e.g., SPSS version 22.0 or Stata).

**Table 2 T2:** Non-inferiority margins.

Outcome measurements	Expected differences	Non-inferiority margin
JOA	<5	5
VAS	<5	5
muscle strength test	<5	5
Sphincter function test	<5	5

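### The primary JOA margin of 5 points is 0.86 SD and does not match the stated 112 per group, so a pass would not support the hypothesis of equivalent efficacy

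*Protocol article*

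**What the plan says.** The design is a two-arm non-inferiority trial of the paraspinal mini-tubular technique (PMTT) against laminoplasty (LP). In section 2.8, "The primary outcome variable is the JOA score", and "The non-inferiority margin for the primary outcome is five". Section 2.9 says that lower scores mean worse function and describes two scales: "The total score of the JOA was 29", with a separate cervical version totalling 17.

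Table 2 in section 2.12 repeats the margin of 5 for JOA. Its column "Expected differences" gives only an upper bound, less than 5, and no planning value. The same 5 also serves VAS, muscle strength and sphincter function.

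Section 2.11 says that "the mean difference and SD for the JOA used in the sample size calculation were as follows: mean 21.7, SD 5.8". It adds a "significance level (alpha) of 0.05" and 90% power, and reports 112 per group, raised to 280 in total for 10% attrition and the circumstances of the centres. It names neither the margin nor the expected difference behind 112. The hypothesis in the Introduction is that PMTT is more cost-effective and that "it is equivalent in safety and efficacy to LP". The Discussion repeats this.

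**The concern.** A non-inferiority margin fixes how much worse the new procedure may be and still pass. Here it is nearly one SD of the primary outcome, and the trial is about four times larger than that margin requires when the procedures do not differ. A large trial with a wide margin has narrow confidence intervals, so PMTT can be shown worse than LP on JOA and still be declared non-inferior. Because the article's hypothesis is equivalent efficacy, such a pass could be reported as confirming something the data contradict. The Discussion expects a confirmed hypothesis to widen the use of PMTT, so what a pass may be taken to mean matters.

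**Working it through.** **Inputs.** Margin 5 (2.8, Table 2). SD 5.8, power 90%, 112 per group, 280 in total, 10% attrition (2.11). Allocation 1:1 (2.4). Evaluable per arm: 280 × 0.9 / 2 = 126.

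**Assumptions.** 5.8 is the common SD of the score. Non-inferiority is judged by the lower limit of the two-sided 95% CI for PMTT minus LP against −5, that is, one-sided 0.025. The article reports 95% CIs but does not state whether alpha is one- or two-sided. All patients are on one scale.

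**1. Margin in SD units.** 5 / 5.8 = 0.86.

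**2. Can 112 be reproduced?** n per group = 2 × [SD × (z(1−α) + z(power)) / (margin − expected loss)]², with z values 1.960 and 1.282.

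| Margin | Expected loss with PMTT | n per group |
|---|---|---|
| 5 | 0 | 2 × (5.8 × 3.242 / 5)² = 28.3, so 29 |
| 5 | 1 | 45 |
| 5 | 2 | 79 |
| 5 | 2.5 | 114 |
| 2.5 | 0 | 114 |
| 2.52 | 0 | 112 |

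At one-sided 0.05, margin 5 with no expected loss needs 24. Solving for the gap at 112 per group: 3.242 × 5.8 × √(2/112) = 2.51 (2.27 at one-sided 0.05). So 112 fixes margin minus expected loss at about 2.5, but not the two values separately.

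**3. What passes at margin 5 with 126 per arm.** SE = 5.8 × √(2/126) = 0.731.
- Largest observed deficit that passes: 5 − 1.96 × 0.731 = 3.57.
- Smallest observed deficit that is significantly worse: 1.96 × 0.731 = 1.43.
- Observed deficits between about 1.4 and 3.6 are therefore both significantly worse and non-inferior.

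**4. Pass probability for a true deficit d.** Φ((5 − d)/SE − 1.96). At 126 per arm it is 0.93 for d = 2.5 and 0.82 for d = 2.9 (half an SD). For d = 2.9 it is 0.77 at 112 per arm and 0.86 at 140. At no true difference it exceeds 0.999 in every case.

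**5. The same trial with margin 2.5, all patients on the 29-point scale.**
- Power at no true difference: Φ(2.5/0.731 − 1.96) = 0.93 at 126 per arm, and about 0.90 at 112.
- True deficit of 1 point: Φ(1.5/0.731 − 1.96) = 0.54 at 126 per arm.
- If cervical patients are analysed separately (their share is not stated, so these are illustrations): 30% cervical leaves 88 per arm and power of about 0.82; 50% leaves 63 per arm and about 0.68.

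**The case against.** Four objections carry weight.

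- **The article is condensed.** A fuller protocol may justify 5. A reader might infer that the sponsor has no rationale, but the article shows only that none is given here. The mismatch between 5 and 112 does not depend on this, because both figures are stated.
- **The size of an important harm is not in the document.** A reader might infer that a clinically important loss would be accepted about 8 times in 10. That rests on taking half an SD (2.9 points) as important, and the article gives no minimal important difference or LP effect to preserve. Frequent passing of deficits inside the margin is how a well-powered non-inferiority test behaves. The objection stands against that reading. It does not rescue the step from a pass to equivalence.
- **112 does not prove that 2.5 was intended.** Margin 5 with an unstated expected loss of 2.5 gives the same 114. Under that reading, moving the margin to 2.5 would cut power at the planned difference to 2.5%. This also stands. However, that reading means planning for a real loss of 2.5 / 5.8 = 0.43 SD with PMTT, which does not fit the hypothesis.
- **2.5 has no clinical basis either.** It follows from the sample size, so it cannot be prescribed as the right margin without the sponsor's clinical judgement.

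A reader might also set 5 against the 7.3 points between 21.7 and 29. The article calls 21.7 part of a mean difference and gives it no time point or scale, so that ratio is not firm enough to use.

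**Conclusion.** The concern holds as an internal mismatch and as a limit on what a pass can mean. The margin of 5 is 0.86 SD. With no expected difference it needs 29 per group, not 112, and the stated size fits a margin minus expected difference of about 2.5. With 126 per arm, observed deficits between about 1.4 and 3.6 points would be both significantly worse and non-inferior, so a pass would not support equivalent efficacy. This rests on 5.8 being the common SD and on the lower 95% limit being the criterion. One-sided 0.05 would make the rule more lenient: the largest passing deficit rises to about 3.8.

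The documents do not show that 5 is clinically wrong, that 2.5 is right, or that tightening is free of cost. The sponsor should settle this before analysis. Confidence is medium, because the full protocol is not shown.

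**What to change.** Before any unblinded analysis, reconcile sections 2.8, 2.11 and Table 2: state one margin and one expected difference, as a number, that together reproduce 112 per group, and say whether alpha is one- or two-sided.

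- **If the expected difference is 0:** replace 5 with about 2.5 points on the 29-point JOA in section 2.8 and the JOA row of Table 2, subject to the sponsor's clinical confirmation. Power at no true difference stays at about 90% to 93% with 112 to 126 per arm, without added patients. The cost is that a true 1-point deficit would pass only about half the time. Power would fall below 90% if 17-point cervical scores are analysed separately.
- **If 5 is kept:** give the clinical reason, state the expected difference, and restate the power (over 99.9% if that difference is 0). Limit the conclusion to PMTT being not worse by 5 or more JOA points, and drop the claim of equivalence from the hypothesis. This costs only text, but the claim is weaker.

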### Primary outcome

2.9.

We will use the JOA score to assess the primary outcome (12, 13). It is divided into the cervical and JOA scores, including subjective symptoms, clinical signs, daily activities, and bladder function. Each item had one or more problems. The total score of the JOA was 29, and the total JOA score of the cervical spine was 17. The lower the score, the more obvious the dysfunction. The outcome parameters will be assessed using validated questionnaires and physical examination. Data from the questionnaires will be collected at 1 week and at 1, 3, 6, 12, and 24 months after the surgery by the research nurse.

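### One raw margin of 5 points covers two JOA scales with maxima of 29 and 17, so what counts as non-inferior depends on the share of cervical patients

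*Protocol article*

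**What the plan says.** Section 2.8 (Outcome measurements) names a single primary variable, "The primary outcome variable is the JOA score", and a single threshold: "The non-inferiority margin for the primary outcome is five". Table 2 repeats that threshold in one JOA row.

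Section 2.9 (Primary outcome) shows that the variable is not one scale: "It is divided into the cervical and JOA scores, including subjective symptoms, clinical signs, daily activities, and bladder function". It then gives the maxima: "The total score of the JOA was 29, and the total JOA score of the cervical spine was 17".

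Section 2.11 (Sample size calculation) uses one set of planning values: "the mean difference and SD for the JOA used in the sample size calculation were as follows: mean 21.7, SD 5.8". Section 2.12 (Statistical analysis) assigns continuous variables to Student's t-test or the Mann-Whitney test, reported as means with SD. Table 1 does not restrict spinal level. Section 2.6 records tumor location at baseline, but section 2.12 gives it no role.

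**The concern.** A fixed number of points is a larger part of a 17-point scale than of a 29-point scale. With one margin for both, the plan tolerates a proportionally greater loss of function in cervical patients. If the two sets of raw scores are also averaged, the difference being tested is a weighted mix whose weights are set by recruitment. The same proportional harm could then fall on either side of the margin according to how many cervical tumors happen to enroll. This touches the primary endpoint and its decision rule, on which the claim of non-inferiority rests.

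The planning figures point the same way. The value 21.7 lies above the cervical maximum of 17, so it cannot describe cervical patients on their own scale. It describes the 29-point scale, or a mix in which that scale dominates.

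**Working it through.** **Inputs.** Maxima 29 and 17 (section 2.9). The lowest possible scores are not given, so proportions below are of the maximum. Margin 5 (section 2.8, Table 2). Planning values "mean 21.7, SD 5.8", "significance level (alpha) of 0.05" with sidedness not stated, power 90%, 112 per group (section 2.11). The cervical share *p* is not given; I assume a range of 0 to 50%.

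**1. The plan's own figure.** n per group = 2 × [SD × (z_alpha + z_power) / (margin − true difference)]². With SD 5.8, margin 5 and true difference 0:
- one-sided 0.025: 2 × (5.8 × 3.242 / 5)² = 28.3, so 29;
- one-sided 0.05: 2 × (5.8 × 2.926 / 5)² = 23.04, so 24.

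The stated 112 is not reproduced. At one-sided 0.025, an unstated distance of 2.5 between margin and true difference gives 114. That discrepancy is a separate matter; it appears here only because step 4 depends on which distance applies.

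**2. The margin on each scale.** 5/29 = 17.2% and 5/17 = 29.4%. The ratio is 29/17 = 1.71. The cervical equivalent of 5 in 29 is 5 × 17/29 = 2.9 points.

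**3. Dependence on case mix.** If PMTT is worse by the same fraction *f* of the maximum in every patient, the true raw difference is *f* × [29(1 − p) + 17p] = *f* × (29 − 12p). The largest uniform loss that stays within the margin is 5 / (29 − 12p).

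| Cervical share | Raw difference at f = 20% | Against margin 5 | Largest uniform loss within margin |
|---|---|---|---|
| 0% | 5.80 | outside | 17.2% |
| 10% | 5.56 | outside | 18.0% |
| 20% | 5.32 | outside | 18.8% |
| 30% | 5.08 | outside | 19.7% |
| 40% | 4.84 | inside | 20.7% |
| 50% | 4.60 | inside | 21.7% |

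At *f* = 20% the crossing point is 29 − 12p = 25, that is p = 1/3. These are true differences, not trial results; they show which side of the null hypothesis the same harm falls on.

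**4. Precision.** Assume that 21.7 and 5.8 describe the 29-point scale alone and that cervical values are proportional: mean 21.7 × 17/29 = 12.7, SD 5.8 × 17/29 = 3.4, gap 8.98. Pooled variance = (1 − p) × 5.8² + p × 3.4² + p(1 − p) × 8.98².
- p = 0.2: 26.91 + 2.31 + 12.90 = 42.12, SD 6.49
- p = 0.3: 23.55 + 3.47 + 16.93 = 43.95, SD 6.63
- p = 0.4: 20.18 + 4.62 + 19.35 = 44.16, SD 6.65

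At one-sided 0.025, the required n per group becomes 36 to 38 instead of 29 with distance 5, or 142 to 149 instead of 114 with distance 2.5.

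**5. Is chance imbalance an extra problem?** Take p = 0.3 and 126 per arm (280 × 0.9 / 2). The variance from unequal cervical shares is 2 × 0.21 × 8.98² / 126 = 0.27. The within-scale variance is 2 × (23.55 + 3.47) / 126 = 0.43. The sum is 0.70, so the standard error is 0.835. This equals 6.63 × √(2/126). The imbalance is already inside the t-test's standard error.

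**The case against.** The strongest reply is that no sentence says the two scales are averaged raw. Section 2.9 describes two scores, section 2.12 is a general list of tests, and a conversion or an analysis by level could sit in an analysis plan that is not shown. This stands as far as it goes: pooling is an inference. It does not rescue the margin, which this article fixes as 5 for the whole primary outcome. If an unseen plan rescales the scores, 5 loses its stated meaning; if it does not, 5 covers two unlike scales.

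Second, the cervical share may be small. Sections 2.5.1, 2.5.2 and 2.10 speak of lumbar lordosis, thoracic kyphosis, lower back fascia, leg pain and lower-limb reflexes. That is a fair limit on size. Cervical tumors are nevertheless eligible, and the cervical score is expressly part of the outcome.

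Third, the precision loss is slight on the stated margin. With SD 6.65, 112 per arm and no true difference, the standard error is 6.65 × √(2/112) = 0.89 and power exceeds 99.9% at one-sided 0.025. This also stands. The loss matters only if the intended distance is nearer 2.5. It disappears if 5.8 already comes from a mixed sample, which the unclear label on 21.7 in section 2.11 does not exclude.

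A reader might infer that an uneven split of cervical patients biases the comparison. The design does not support that: randomization leaves the raw difference unbiased for the mix-weighted effect, and step 5 shows that imbalance and the larger SD are one and the same variance term. A reader might also infer that the margin is laxest exactly where the spinal cord is at risk. The Introduction describes cord compression for these tumors in general, so the documents do not single out cervical patients.

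**Conclusion.** The point holds for the margin and for the meaning of the estimate. One raw margin of 5 allows 17.2% of the maximum on one scale and 29.4% on the other. Under the comparison that the article implies, a uniform 20% loss lies outside the margin below a cervical share of one third and inside it above. The percentages follow directly from stated figures. The case-mix result assumes raw pooling and a loss that is the same fraction of the maximum in every patient.

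The rise in SD from 5.8 to about 6.5 to 6.65 is secondary. It rests on an assumed cervical share of 20 to 40%, proportional cervical values, and planning figures taken from the 29-point scale alone. It is lost precision, not bias, and it shrinks if few cervical patients enroll. The margin should be corrected before unblinding because the primary conclusion depends on it.

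**What to change.** Before unblinding, choose one of two routes:

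- **Common scale.** Express the primary variable as a percentage of the maximum of the patient's own scale, with one margin justified on that scale. The proportional equivalent of the stated margin is 5/29 = 17.2%, or 2.9 cervical points. This only translates the existing figure, and the sponsor must justify the value. The route treats equal percentages on the two instruments as comparable, which should be argued.
- **Separate margins.** Keep raw points and set a justified margin for each scale.

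Under either route, include scale (cervical versus other) as a term in the primary model, report the effect on each scale, state which scale thoracic tumors use, and recheck the sample size with the matching SD. Under the proportional assumption the common scale keeps the planned ratio of margin to SD: 17.2% against 5.8/29 = 20%, or 0.86, the same as 5/5.8.

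The cost is modest. JOA scores and tumor location are already recorded, so no new data are needed, and the randomization need not change. The margin and the sample-size statement must be restated. On the first route, the result is in percent of scale rather than in familiar raw points.

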### Secondary outcome

2.10.

Secondary outcomes include the gross tumor resection(GTR) rate, tumor recurrence rate, VAS, assessment of back and leg pain at rest, physical examination, length of hospital stay, expenses, and complications. One of the secondary outcomes was the VAS of pain. Perceived pain intensity was measured using the VAS score [pain scale ranging from 0 (no pain) to 100 mm (the worst pain imaginable)] (14). The pain will be assessed because most patients have pain in different regions. A physical examination will be conducted at 1, 6, and 12 months after the surgery. This will include the sphincter function test, muscle strength exercise, patellar and Achilles tendon reflex assessment, and sensory assessment of the affected spinal region. Muscle strength will be scored on a scale ranging from zero (no contraction) to five (normal muscle strength) (15).

The cost-effectiveness of the hospital stay will be evaluated by summarizing the cost of the surgical procedure and the number of days before discharge. The cost of the additional procedures in case of complications will be added to the total cost of the patient's hospital stay. The primary cost of treatment will include the cost of hospital admission, surgery, medication, rehabilitation, and other healthcare utilization. The details of these charges will be registered in a diary. Immediately after the operation, a systematic assessment of complications (including cerebrospinal fluid leakage, venous thromboembolism, wound infection, urinary tract infection, hematoma, and progressive neurological deficit) will be conducted by the surgeon and research nurse until patient discharge. Surgical data will include intraoperative spinal cord and nerve root injury, operative time, and intraoperative blood loss.

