## Discussion

3.

The FJMUUH05 trial is a multicenter RCT, the first RCT of surgery for spinal IDEM tumors. To date, similar RCTs have not been reported on this topic. The trial was approved by the Chinese Clinical Trial Registry (ChiCTR, www.chictr.org.cn). The trial hypothesis is that PMTT has superior cost-effectiveness and is equivalent in safety and efficacy to LP for treating spinal IDEM tumors.

Tubular spinal surgery has gained significant prominence because of the development of minimally invasive technologies and instruments. The tubular retractor is inserted to reach the operation field by separating the paravertebral muscle and exposing the pathological lesions. This technology allows surgeons to remove tumors with two-handed operations and simultaneously use multiple microscopic instruments. Moreover, intraoperative three-dimensional imaging is another massive shift from endoscopic technology, which lets the operator conveniently operate the imaging apparatus, thereby reducing the complication rates of dural rupture. Compared with traditional surgery, fewer clinical studies have been conducted on the selection of surgical indications. The safety and effectiveness of the operation and the treatment of complications during and after the operation lack a unified opinion. The patients will be randomized to the PMTT or LP groups after tumor resection. The trial aims to study the clinical results of PMTT vs. LP for spinal IDEM tumors. This RCT study provides high-quality evidence for the efficacy of tubular spine surgery for spinal IDEM tumors. We believe that the FJMUUH05 trial will provide useful information on the long-term effects of the two treatments for spinal IDEM tumors. To date (October 2021), 11 patients have been included in the trial.

In conclusion, the FJMUUH05 trial is a multicenter RCT investigating the cost-effectiveness, safety, and effectiveness of PMTT and LP in spinal IDEM tumors. When this trial is completed with the hypothesis confirmed, it will popularize the application of PMTT and improve patient outcomes.

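### Cost-effectiveness is part of the main hypothesis, but the stated evaluation summarises costs and hospital days and never relates them to a measure of effect

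*Protocol article*

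**What the plan says.** The Introduction sets the hypothesis: "The main hypothesis is that PMTT has advantages in cost-effectiveness, and it is equivalent in safety and efficacy to LP". The Discussion repeats it in stronger terms: "The trial hypothesis is that PMTT has superior cost-effectiveness and is equivalent in safety and efficacy to LP for treating spinal IDEM tumors".

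The economic outcomes are secondary. Under Outcome measurements: "The secondary outcome variables include the VAS score, physical examination findings, length of hospital stay, expenses, and complications".

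The Secondary outcome section gives the evaluation: "The cost-effectiveness of the hospital stay will be evaluated by summarizing the cost of the surgical procedure and the number of days before discharge". It then adds cost items. On complications: "The cost of the additional procedures in case of complications will be added to the total cost" of the hospital stay. On the wider bill: "The primary cost of treatment will include the cost of hospital admission, surgery, medication, rehabilitation, and other healthcare utilization". On the source: "The details of these charges will be registered in a diary".

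The Statistical analysis section names Student's t-test or the Mann–Whitney U test, one of which, as a "test will be used to compare continuous variables". It describes no analysis that takes cost and effect together.

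**The concern.** A cost-effectiveness claim needs two quantities: the difference in cost between the arms and the difference in effect. The stated evaluation contains only the first. A reader who follows the article will obtain costs and lengths of stay by arm, compare them, and have nothing that says what was gained or lost in neurological function for the money.

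This is more than detail left to a fuller document. The article says how cost-effectiveness will be evaluated, and the method it gives answers a different question from the hypothesis. A later plan would have to replace that sentence, not merely fill it in.

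At stake is one of the trial's headline claims. The Discussion expects a confirmed hypothesis to widen the use of PMTT. If PMTT proved cheaper and somewhat worse on JOA within the margin, the stated evaluation would show only the saving.

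**Working it through.** The documents give no figure for cost or cost-effectiveness, so there is none to reproduce. The sample size of 112 per group rests on JOA alone. The check is therefore a reading of the sections side by side, plus one calculation on what non-inferiority would establish.

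**Step 1: is there an effect term?** The items named in the economic paragraph of the Secondary outcome section are:
- procedure cost: a cost;
- days before discharge: resource use;
- additional procedures for complications: a cost;
- admission, surgery, medication, rehabilitation and other use of care: costs.

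None is an effect. JOA, VAS and the other clinical outcomes are defined elsewhere, and no sentence links them to cost. No ratio, net benefit or other joint summary is named.

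**Step 2: does the analysis section supply the link?** It compares variables one at a time between two groups. Cost would be compared on its own and JOA on its own.

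**Step 3: which cost total tests the hypothesis?** The evaluation sentence concerns the hospital stay, up to discharge. The later sentence on treatment cost includes rehabilitation and other use of care, which can fall after discharge. Follow-up lasts two years. The article does not say which total carries the hypothesis, or over what period.

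**Step 4: would JOA non-inferiority make cost alone sufficient?** If effect were equal, lower cost would settle the matter. Inputs:
- non-inferiority margin 5 (Outcome measurements; Table 2);
- SD 5.8 and 112 per group (Sample size calculation);
- 95% confidence interval (Statistical analysis).

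Standard error of the difference = 5.8 × √(2/112) = 5.8 × 0.1336 = 0.775.

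Half-width of the 95% interval = 1.96 × 0.775 = 1.52 points.

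Largest observed PMTT deficit that still passes = 5 − 1.52 = 3.48 points.

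An observed deficit between 1.52 and 3.48 points would therefore meet non-inferiority while its interval excluded zero. PMTT would be declared non-inferior and also shown to be worse.

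The margin is also large relative to the scales given under Primary outcome: 5/29 = 17% of the full JOA score and 5/17 = 29% of the cervical version.

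**Step 5: what follows for cost.** Let S be the mean saving with PMTT and d its JOA deficit. The stated evaluation reports S, and S is the same whether d is 0 or 3.48. Whether S is worth having depends on d, which the evaluation leaves out.

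**The case against.** The strongest reply is that the hypothesis pairs the cost advantage with equal safety and efficacy, so a lower cost would support a cost-minimisation argument. JOA is collected to 24 months and would be reported beside cost, so nobody would be kept from seeing a deficit. Part of this stands: the question can be answered from the kind of data planned, and it would be wrong to call it untestable. But the article does not state the cost-minimisation route, and step 4 shows that non-inferiority within 5 points does not establish the equal effect that the route needs.

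A reader might go further in several ways that the documents do not support:
- **That only procedure cost and hospital days are counted.** The same paragraph adds complications, admission, medication, rehabilitation and other use of care. The cost list is broad; what is missing is the effect.
- **That hospital days are double-counted with admission cost.** Summarising can mean reporting the two separately, and length of stay and expenses are listed as separate outcomes. Nothing says that days are converted to money or added to it.
- **That skewed costs would be analysed by Mann–Whitney, so that mean costs are never compared.** The article allows a t-test or Mann–Whitney for continuous variables in general and assigns neither to cost. Any size put on this would rest on assumed cost distributions, since no cost data are given.

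The hospital-stay and treatment-cost sentences can also be read as a narrower and a wider item in sequence. That reading is fair, and it removes any outright contradiction. It still leaves open which total tests the hypothesis.

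**Conclusion.** The concern holds in this limited form. The hypothesis claims better cost-effectiveness; the stated evaluation compares costs and resource use and never relates them to effect. Followed as written, it cannot by itself support a cost-effectiveness conclusion.

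The consequence for the economic result cannot be quantified from the documents. What can be sized is the room that non-inferiority leaves: an observed PMTT deficit of up to about 3.5 JOA points would pass. That figure assumes 112 analysed per group, that the SD of 5.8 applies to the analysed score, and that the two JOA versions are treated as one scale, as the single margin of 5 implies. Those assumptions affect the figure, not the finding, which rests on the text.

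The fault lies in a secondary outcome that carries a headline claim. The primary JOA comparison is not affected.

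**What to change.** Choose one of two routes and write it into the plan before the data are analysed.

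**Route A, keep the claim.**
- State which cost total tests the hypothesis (the hospital stay alone, or the wider treatment cost recorded in the diary) and over what period.
- Report the difference in arithmetic mean cost with a 95% confidence interval.
- Report it jointly with the JOA difference, for example by bootstrapping incremental cost and incremental effect together.
- Put the 17-point and 29-point JOA versions on a common scale first, for example as a percentage of the maximum, so that a point means the same for all patients.

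**Route B, narrow the claim.** Rename the outcome a cost comparison and remove cost-effectiveness from the hypothesis and the conclusion.

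Route B costs only wording and a narrower conclusion. Route A costs some analysis work and no extra patients, and its effect data are already planned. Whether it needs more cost data depends on the period chosen. The article does not say how long the diary is kept, so a cost total running to 24 months should not be promised until that is confirmed.
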